#### Randomization & blinding

After baseline data have been collected and participants have dispersed, we utilize a computerized randomization procedure stratified by site and gender to assign participants to either the intervention or the control (wait-list) arm. The randomization procedure is programmed into Research Electronic Data Capture (REDCap), a secure web application for building and managing online surveys and databases [32]. A randomization allocation table was created using random permuted blocks with randomized block sizes 2, 4, 6 and is uploaded into REDCap. Smaller block sizes are used to distribute participants within either group as evenly as possible.

One designated research assistant is un-blinded for the duration of the study and works with senior center staff to schedule the WTW intervention sessions. Senior center staff call participants to inform them of their scheduled intervention session. While the case manager group leaders administer WTW, the same un-blinded research assistant attends sessions to take attendance and monitor fidelity to the curriculum using a standardized checklist of all the major teaching points of each intervention session (see Additional file 1: Appendix A). Other (blinded) project staff members maintain regular telephone contact with participants in both arms of the study to remind them to wear their pedometers but without explicitly prompting physical activity or walking. Project staff who are in the field collecting data are blinded to the participant assignment group for the entire study duration.

All participants in both the intervention and control groups receive the same frequency of contact from study staff (phone call reminders) and the same incentives (pedometers, $25 visa gift card at each data collection time point). We do not refer to the control group as a “wait-list” when speaking with participants and agency staff, but rather refer to that group by the month in which they will start the WTW program, for example, we will compare the “January” group with the “April” group.

### Study assignments

#### Intervention group

Participants assigned to the intervention group immediately attend the group-based interactive behavioral stroke risk reduction walking intervention led by an in-house case manager after baseline (T0). In addition to reminder phone calls prior to each intervention session, efforts to increase retention and sustain participation in the intervention include scheduling transportation for participants when applicable, as well as notifying participants that attendance will be taken at each session.

#### Wait-list control group

Participants assigned to the wait-list control group are invited to participate in WTW after follow-up data collection is completed 3 months from baseline (they do not repeat outcome measures at this time). As previously mentioned, control group participants are also given pedometers by blinded RAs, receive the same reminders to wear them, have follow-up data collected at the same time points, and have the same frequency of contact with study personnel as the intervention group throughout the study duration.

### Measurements

#### Data sources

Data sources include FITBIT® Zip pedometers [33], surveys, physical exams, and fingerpricks. The surveys, physical exams, and fingerpricks are administered with each individual at the senior centers by trained bilingual study staff. Surveys are interviewer-administered using REDCap [32], accessed using iPads with internet access. Survey instruments were translated into the native languages of our targeted ethnic groups (Spanish, Mandarin and Korean) a priori through a professional translation company; the accuracy of translations was verified by bilingual study staff as well as by seniors with whom the surveys were piloted prior to trial implementation. Pedometer data are downloaded using the iPads and stored/accessed through the secure FITBIT® website at each data collection time point. All study outcomes, collection time points, and data sources are listed in Table 1.

#### Primary outcomes

The primary outcome measure is change in walking level from baseline (T0) to 1 and 3 months (T1 and T2) as measured by the FITBIT® Zip pedometers. Physical activity level is supplementarily assessed using the International Physical Activity Questionnaire [34] included in the survey at all three time points. Stroke risk factor knowledge is assessed via survey using the Stroke Action Survey and questions developed by Pancioli et al. [35, 36]. We measure self-efficacy for reducing stroke risk and increasing physical activity. Self-efficacy is best captured by measuring both self-efficacy expectations and outcome expectations [21]. As such, we measure self-efficacy expectations with the General Self-Efficacy Scale [37] and a modified version of the Chronic Disease Self-Efficacy Scale [38] that focuses on self-efficacy for stroke risk reduction; outcome expectations for being physically active is assessed using the Outcome Expectations for Exercise Scale [39].

#### Secondary/exploratory outcomes

To explore the relationship between the intervention and biological markers of health, we collect height and weight in light clothing without shoes at all three data collection time points in strict accordance with standardized procedures we have used previously. A random 5 % of participants will have their weight and height measured by two different research assistants so that inter-rater reliability can be calculated. To assess our main secondary outcome measure—systolic blood pressure—trained staff implement a standard, seated blood pressure protocol based on current Joint National Committee on Prevention, Detection, Evaluation, and Treatment of High Blood Pressure (JNC 7) guidelines, but allowing a 5-min rest between each measure [40]. Point-of-care CardioChek meters are used to measure cholesterol (using the Lipid Panel strip), which require only a small capillary blood sample (from a fingerprick). We use dried blood spots to obtain assays for HgA1c and CRP, also collected by fingerpricks. So that we can explore whether the intervention influenced healthcare seeking to control stroke risk factors, we ask participants to report on visits to healthcare providers in the previous three months at baseline and 3 months [41].

#### Other exploratory outcomes and covariates

Other measures being collected are listed in Table 1. These include exploratory outcomes that might be influenced by the intervention such as health-related quality of life [42] and stress [43]. In addition, we will measure constructs such as acculturation level [44] and neighborhood walkability [45] that, while not linked explicitly to specific aims, are considered to be critical covariates likely to be associated with outcomes and can also be used to evaluate the success of the randomization.

### Sample size and power

As described above, our primary outcome of interest is change in mean steps/day, while our main secondary outcome measure is change in systolic blood pressure. Based on our capacity, we plan to enroll 240 subjects from 4 senior centers. From our previous senior center research we estimate that as many as 15 % of subjects will not complete follow-up. Data from our previous senior center studies of older Latinos and African Americans showed mean steps/day 2713 (std. dev. 2190) and mean SBP 141 mm Hg (std. dev. 20 mm Hg); intra-class correlation within senior centers was at 0.0085. Since we propose a repeated measures design with 3 repeated measurements [46], the underlying statistical power of the study comes from two dimensions of observations: the number of unique subjects and the number of repeated measurements within a subject. Based on sample size/power analytic methods for repeated measures analysis [47, 48], using a 2-sided test with a type I error of 0.05, and a type II error of 0.2 (power 80 %), and assuming an average 2.7 data points per subject and an auto-correlation at 0.2 level, after adjusting for clustering, the effective sample size will be 96 subjects in each arm, which will enable us to detect effect sizes as small as 581 steps/day (far below a clinically meaningful increase of 5000 steps/day [49]) and 5.3 mm Hg. A decrease of 5 mm Hg substantially decreases stroke risk [50] and is comparable to effect sizes observed in walking interventions of similar intensity [51].

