#### Comparing baseline characteristics of intervention and control arm subjects

Using t-tests for continuous variables and chi-square tests for categorical variables, we will compare the two groups on baseline characteristics to measure the success of the randomization: 1) sociodemographic characteristics; 2) mean steps/day over 1 week in the window post screening and distribution of pedometers, to the T0 baseline data collection one week later; 3) systolic blood pressure, body mass index, non-HDL cholesterol, HgA1c; 4) stroke knowledge, self-efficacy. Since steps/day is a continuous variable, at each time-point (30 days/T1 and 90 days/T2) we will perform a simple descriptive cross-sectional analysis of mean change in scores between baseline and follow-up in each treatment arm. In our primary analyses, we will test the statistical significance of the unadjusted difference in change-scores between the groups using t-tests for symmetrically distributed data and analogous nonparametric tests such as the Wilcoxon sign rank tests for data that are skewed. Imbalance between the treatment arms of characteristics described above would inflate the standard error, making the unadjusted analyses appropriately conservative; therefore, the unadjusted analyses will serve as the primary results of the trial. If, however, we did identify chance differences between the treatment arms in the distribution of the baseline level of the outcome, then we will also conduct secondary analyses in which we will use multivariate modeling, such as analysis of covariance, to adjust for these factors. The adjusted means of the change-scores from multivariate models will be compared and tested between the two arms, and will also be compared with the unadjusted means to assess the influence of these factors on endpoints. As sensitivity analyses, we will also examine the difference between groups in the absolute steps/day (instead of the change-score), adjusting for baseline. These sensitivity analyses will allow us to compare outcomes between groups without assuming linearity of effect across different baseline levels of physical activity. Using multivariate modeling, we will also test interactions between treatment arm and selected effect modifiers (e.g., age, level of acculturation, etc.) to identify sub-groups of participants who improve more than other groups. Since this trial is not designed with power to examine these subgroups, these analyses will be exploratory and hypothesis-generating in nature. Finally, we will assess changes in steps/day between baseline and the end of the intervention period, and differences between the control and intervention groups in steps/day trajectories over time. These analyses will consist of graphical analysis and parametric statistical testing using repeated measures mixed effects models [55, 56]. To determine the extent to which increases in stroke knowledge and self-efficacy mediate improvements in steps/day, the variation (R-squared) in increase in steps/day is explained by variation in increase in the stroke knowledge and self-efficacy constructs will be calculated [57, 58]. Analysis of the effect of the intervention on all the secondary and exploratory outcomes will follow the same analysis.

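### The stated 80% power for 581 steps/day (5.3 mm Hg) belongs to an average over three measurements including baseline, not to the change-score t-test declared primary

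*Protocol article*

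**What the plan says.** Under *Sample size and power* the Protocol article says "our primary outcome of interest is change in mean steps/day", with change in systolic pressure as the main secondary outcome. The inputs are "mean steps/day 2713 (std. dev. 2190") for steps, an SD of 20 mm Hg for systolic pressure, an intra-class correlation of 0.0085, 15% loss to follow-up, three repeated measurements, an average of 2.7 "data points per subject and an auto-correlation at 0.2", "using a 2-sided test with a type I error of 0.05", and "a type II error of 0.2 (power 80"%). With 96 effective subjects per arm it concludes "which will enable us to detect effect sizes as small as 581" steps/day, and 5.3 mm Hg.

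Under *Primary outcomes*: "The primary outcome measure is change in walking level from baseline (T0) to 1 and 3 months (T1 and T2"). *Methods/Design* places T0 before randomization.

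Under *Comparing baseline characteristics of intervention and control arm subjects*, the primary analyses will "test the statistical significance of the unadjusted difference in change-scores between the groups using t-tests", with nonparametric tests for skewed data. That section says the unadjusted analyses are the trial's primary results. Analysis of covariance is secondary, follow-up steps adjusted for baseline is a sensitivity analysis, and repeated-measures mixed models come last, for trajectories.

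**The concern.** The power figure and the primary test belong to different analyses, and the correlation acts in opposite directions in them. When several measurements are averaged, low correlation helps because each one adds nearly independent information. In a change score, low correlation hurts because subtracting baseline adds its noise: the SD of a change exceeds the cross-sectional SD whenever the correlation is below 0.5. Assuming 0.2 therefore favours the calculation and penalises the declared test. In addition, T0 precedes randomization, so a group difference averaged over T0, T1 and T2 is not a treatment effect.

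At stake is how the result is read. A reader who relies on the power section would treat a non-significant result as informative about effects near 600 steps/day or 5 mm Hg, when the primary test may have little chance of detecting them.

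**Working it through.** **Inputs, all from *Sample size and power*:** SD 2190 steps/day and 20 mm Hg; correlation r = 0.2; n = 96 effective per arm; two-sided 0.05 and 80% power, so z = 1.960 + 0.842 = 2.802. The article gives no SD of change and no other correlation.

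**Formula.** Detectable difference = 2.802 × SD × √(2f/n), where f is the variance of the analysed quantity relative to one measurement. At n = 96 this is 885.6 × √f steps/day.

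**1. Reproducing 581.** For the mean of three AR(1) measurements, f = (3 + 4×0.2 + 2×0.04)/9 = 0.4311. The result is 581.5 steps/day and 5.31 mm Hg. Other forms at n = 96 miss:

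| Form | f | Steps/day |
|---|---|---|
| Three measurements, exchangeable | 0.467 | 605 |
| 2.7 measurements, AR(1) | 0.471 | 608 |
| 2.7 measurements, exchangeable | 0.496 | 624 |
| T1 and T2 only | 0.600 | 686 |
| One follow-up | 1.000 | 886 |

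The systolic figure is not a second confirmation: 581/2190 and 5.3/20 are both 0.265 SD.

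**2. The declared test.** For a change score, f = 2(1 − r) = 1.6, so the SD of change is 2190 × √1.6 = 2770. The standard error is 2770 × √(2/96) = 399.8. Power at 581 is Φ(581/399.8 − 1.960) = 0.306. The detectable difference is 2.802 × 399.8 = 1,120 steps/day, or 10.2 mm Hg. For the T2 change under AR(1), r = 0.04 and f = 1.92, giving 26% power and 1,227 steps/day.

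**3. Dependence on r (n = 96).**

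| r | Power at 581 | Steps/day | mm Hg |
|---|---|---|---|
| 0.2 | 31% | 1,120 | 10.2 |
| 0.5 | 45% | 886 | 8.1 |
| 0.7 | 66% | 686 | 6.3 |
| 0.785 | 80% | 581 | 5.3 |

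**4. Dependence on n.** With 120 × 0.85 = 102 completers per arm and no clustering reduction, r = 0.2 gives 32% and 1,087 steps/day. The conclusion does not turn on the value 96.

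**5. Attrition (minor).** The stated 2.7 equals 1 + 2×0.85, so it reflects the 15% loss, but 581 needs 3.0 measurements; 2.7 gives 608–624. The 96 matches 120/(1 + 29×0.0085) = 120/1.2465 = 96.3, that is, full enrolment in arm-by-site clusters of 30.

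**6. Figures with clustering and loss both applied.** Assume 102 completers per arm over four sites, 25.5 per cluster: n = 102/(1 + 24.5×0.0085) = 102/1.20825 = 84.4, and 2.802 × 2190 × √(2/84.4) ≈ 944.
- Change score, r = 0.2: 944 × √1.6 ≈ 1,195 steps/day; 10.9 mm Hg.
- Change score, r = 0.8: 944 × √0.4 ≈ 597 steps/day; 5.5 mm Hg.
- Baseline-adjusted, one time point, r = 0.2: f = 1 − 0.04 = 0.96, about 925 steps/day.
- Baseline-adjusted, T1/T2 mean, r = 0.2: f = 0.6 − 0.2² = 0.56 (exchangeable) or 0.6 − 0.12² = 0.5856 (AR(1)), about 707 to 723 steps/day.

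**The case against.** **The 31% rests on one reading of 0.2.** The article calls it an auto-correlation and cites methods not shown here; it is not labelled as the baseline-to-follow-up correlation. This stands, so the figures must be conditional on r. It does not rescue the claim: 581 for the change-score test needs about 0.785, far from the only correlation stated.

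**The repeated-measures model could be the intended basis for power.** The analysis section says otherwise. Nor would using T0 properly, as a covariate, recover 581: at n = 96 the baseline-adjusted T1/T2 mean gives 885.6 × √0.56 = 663 to 885.6 × √0.5856 = 678 steps/day.

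**The origin of 96 is not stated.** Correct. Completers alone in clusters of about 8.35 also give 102/(1 + 7.35×0.0085) = 96.0. A reader might take it as established that the 15% loss was left out; the document gives no cluster size, so this is only an inference. The gap between 581 and 608–624 is also small.

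**The trial is not underpowered for what matters.** A reader might infer that it cannot detect a clinically meaningful increase in walking, or that enrolment is wrong. Neither is supported. The article's benchmark is 5000 steps/day, far above any detectable difference computed here, and the 240 was set by capacity rather than derived from 581. The argument is weaker for systolic pressure, where the article itself cites 5 mm Hg as lowering stroke risk and as comparable to effects in similar walking interventions.

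**A null result would be judged by its confidence interval.** It should be, and that limits the harm. The stated power is still wrong for the declared test.

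**Conclusion.** The concern holds as a mismatch between the stated power and the declared primary analysis. Of the forms tried at n = 96, only the three-measurement AR(1) average reproduces the published figures, and it counts a pre-randomization value as an outcome.

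Conditional on 0.2 being the baseline-to-follow-up correlation, the T1 change-score test falls from the stated 80% to about 31% power at 581 steps/day, and its detectable difference nearly doubles. For systolic pressure the detectable difference is about twice the 5 mm Hg cited as relevant; power at 5 mm Hg is Φ(5/3.65 − 1.960) ≈ 28%, with standard error 20 × √1.6 × √(2/96) = 3.65. At higher correlations the shortfall narrows, closing at about 0.785.

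These figures are normal approximations for the t-test. The rank-test alternative for skewed data was not evaluated.

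**What to change.** In *Sample size and power*, replace 581 steps/day and 5.3 mm Hg with detectable differences for the test that will be primary. Count only T1 and T2 as outcomes, apply both clustering and the 15% loss, and state the cluster size used.

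- **Keeping the change-score t-test primary:** on the assumed clusters of 25.5, state about 1,195 steps/day and 10.9 mm Hg at r = 0.2, with the range over r = 0.2 to 0.8 (down to about 597 steps/day and 5.5 mm Hg).
- **Promoting the already planned baseline-adjusted analysis to primary:** on the same n and r = 0.2, state about 925 steps/day for one time point, or 707–723 for the T1/T2 mean, and amend the analysis section to match.

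Either route resolves the mismatch; the second gives a smaller detectable difference at r = 0.2. The cost is one rewritten paragraph, plus a change to the analysis section under the second route, and a less favourable stated detectable difference. No extra participants are needed.

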**Methods/Design:**

In this randomized single-blind wait-list control study, high-risk ethnic minority seniors are enrolled at senior centers, complete baseline data collection, and are randomly assigned to receive the intervention “Worth the Walk” immediately (*N* = 120, intervention group) or in 90 days upon completion of follow-up data collection (*N* = 120, control group). Trained case managers employed by the senior centers implement hour-long intervention sessions twice weekly for four consecutive weeks to the intervention group. Research staff blinded to participants’ group assignment collect outcome data from both intervention and wait-list control participants 1 and 3-months after baseline data collection. Primary outcome measures are mean steps/day over 7 days, stroke knowledge, and self-efficacy for reducing stroke risk. Secondary and exploratory outcome measures include selected biological markers of health, healthcare seeking, and health-related quality of life. Outcomes will be compared between the two groups using standard analytic methods for randomized trials. We will conduct a formal process evaluation to assess barriers and facilitators to successful integration of Worth the Walk into the aging services network and to calculate estimated costs to sustain and scale up the intervention. Data collection is scheduled to be completed in December 2016.

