### Worth the Walk intervention: conceptual basis and development

The Worth the Walk intervention is culturally-tailored and based in social cognitive theory [21, 22] and attribution theory [23, 24]. It incorporates elements such as verbal persuasion, goal setting, problem solving, and attribution retraining techniques that encourage participants to modify their expectations for aging (i.e., teach older adults not to attribute mutable stroke risk factors to aging) and change their own behavior to reduce stroke risk. In a previous National Institute on Aging-funded RCT of a behavioral intervention to increase walking—¡Caminemos! (R01 AG024460-05) [25, 26]—our team enrolled 572 older Latinos from 27 community senior centers and randomized them to receive either an attribution retraining intervention teaching not to attribute sedentary lifestyle to old age, or an active control group (series of lectures). We followed participants for 24 months; the intervention successfully increased walking levels (mean increase 6207 steps/day) more than the control group (*p* = 0.04). Though this efficacy study succeeded in meaningfully increasing walking levels, the intervention delivery was supported by National Institutes of Health (NIH) funding of research staff, limiting the intervention’s sustainability. With the current effectiveness trial, we have adopted many components of the Caminemos intervention, linking them with stroke and stroke risk factor education to create a new culturally-tailored intervention, and have integrated the new intervention directly into senior center programming without relying on NIH-funded staff for implementation (essentially making the efficacy-to-effectiveness transition). Our study builds on the expertise our team acquired in conducting the Caminemos trial, including recruitment, retention, screening and enrollment protocols, pedometer training, and group leader training (see below).

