Though multifaceted (including both formal stroke education and behavioral change strategies), this intervention is intentionally designed to be low-cost, sustainable and scalable. We chose to use in-house AAA-funded case managers rather than professional healthcare providers because a major goal of this project is to evaluate a practical and sustainable intervention that can be scaled up across the national aging services network; thus, even a modest stroke risk factor reduction in physical activity or blood pressure could have a tremendous population impact on preventing strokes and decreasing stroke disparities. Upon completion of this trial, we will have trained a cadre of senior-center based case managers in a new skill set of health disparities intervention implementation that can be used not only for stroke risk factor reduction interventions but also other evidence-based health promotion programs.

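### The plan's reassurance about its sensitivity for steps/day sets 581 beside a 5000 benchmark that is out of scale with its own mean of 2713 (SD 2190), and 581 is not the detectable difference for the primary change-score test

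*Protocol article*

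**What the plan says.** All references are to the protocol article.

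- **Sample size and power.** Enrolment is set by what the sites can handle: "Based on our capacity, we plan to enroll 240 subjects from 4 senior centers". The planning values from the team's earlier senior-center work are "mean steps/day 2713 (std. dev. 2190) and mean SBP 141 mm Hg (std. dev. 20 mm Hg". The calculation is described as "using a 2-sided test with a type I error of 0.05, and a type II error of 0.2 (power 80" percent), with an average of 2.7 data points per subject, an autocorrelation of 0.2 and, after the clustering adjustment, an effective 96 per arm. The result is a detectable 581 steps/day, which the text calls "far below a clinically meaningful increase of 5000" steps/day, citing reference 49.
- **Worth the Walk intervention: conceptual basis and development.** Of the team's earlier trial in 572 older Latinos at 27 centers, the text says "the intervention successfully increased walking levels (mean increase 6207" steps/day), more than in the control group, p = 0.04.
- **Comparing baseline characteristics of intervention and control arm subjects** (under Statistical analyses). The primary results are unadjusted between-group comparisons of change scores by t-test, or by a nonparametric analogue if the data are skewed.
- **Multiple comparisons.** Change in steps/day is the primary endpoint.

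Nowhere is 5000 explained or reconciled with 2713 (SD 2190).

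**The concern.** A benchmark of 5000 steps/day means that the average participant would go from 2713 to 7713 steps/day. The other benchmark in the same paragraph, 5 mm Hg against an SD of 20, is 0.25 SD; this one is 2.28 SD. The two were plainly not chosen on comparable grounds.

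Because enrolment is fixed by capacity, the comparison of the detectable with the meaningful effect is all that the article offers to show that the trial is sensitive enough on its primary endpoint. Both sides of that comparison are doubtful: 5000 does not fit the baseline data, and 581 belongs to a different analysis from the one named as primary. Readers will use 5000 as the yardstick for the result. They will also rely on the 581 figure if the trial finds no difference and they ask what it could have missed.

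**Working it through.** **Inputs** (Sample size and power unless noted): two-sided alpha 0.05 and power 80%, so 1.960 + 0.842 = 2.802; SD 2190; mean 2713; 120 per arm over 4 centers, so 30 per arm per center; ICC 0.0085; autocorrelation 0.2; 3 measurements; effective n 96 per arm. From the account of the earlier trial: 572 people, 27 centers, 6207 steps/day, p = 0.04.

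**1. Reproducing the plan's figures**
- Effective n: 120 / (1 + 29 × 0.0085) = 120 / 1.2465 = 96.3.
- Variance factor for the mean of 3 measurements under first-order autocorrelation of 0.2: [3 + 2(2 × 0.2 + 0.04)] / 9 = 0.431.
- Detectable difference: 2.802 × 2190 × √(2 × 0.431 / 96) = 581.5 steps/day. With SD 20 it is 5.31 mm Hg.
- Both stated figures reproduce, and 5000 enters neither. Using 2.7 points instead of 3 gives 608 (first-order autocorrelation) or 624 (equal correlation), so 581 corresponds to 3 full measurements.

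**2. The benchmark against the baseline**
- 5000 / 2713 = 1.84; 5000 / 2190 = 2.28 SD; 5000 / 581 = 8.6.
- A plain two-sample comparison would need about 4 people per arm to detect such a difference.

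**3. The earlier trial's 6207**

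Assumptions: equal split (286 per arm) and the planning SD of 2190, or a change-score SD of 2770 (derived in step 4), with or without a design effect of 1 + (572/27 − 1) × 0.0085 = 1.17.
- Relative to baseline: 6207 / 2713 = 2.29; 6207 / 2190 = 2.83 SD.
- Read as a between-arm difference with SD 2190: SE = 2190 × √(2/286) = 183, so z = 6207 / 183 = 34. Across the SD and design-effect variants z is 25 to 34, against 2.05 for p = 0.04. To give p = 0.04 the SD would have to be 6207 / (2.054 × √(2/286)), about 36,000 steps/day.
- Read as a within-arm increase: p = 0.04 implies an arm difference of 2.054 × 183 = 376, or up to 515 across the variants. The control arm would then have gained 6207 − 515 = 5692 to 6207 − 376 = 5831 steps/day, so both arms would have more than tripled from 2713.
- Neither reading fits a population averaging 2713 (SD 2190).

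**4. Detectable difference for the primary change-score comparison**

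Change-score SD = 2190 × √[2(1 − r)]; detectable difference = 2.802 × that SD × √(2/96).

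| Correlation r of baseline with follow-up | Change-score SD | Detectable difference (steps/day) |
|---|---|---|
| 0.2 (the plan's value) | 2770 | 1,120 |
| 0.5 (assumed) | 2190 | 886 |
| 0.8 (assumed) | 1385 | 560 |

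**5. Illustration only: if 5000 and 6207 were weekly totals (assumption)**
- 5000 / 7 = 714 steps/day (0.33 SD, 26% of the mean); 6207 / 7 = 887 steps/day (0.40 SD).
- 581 / 714 = 81%. The detectable 1,120 and 886 from step 4 would exceed 714; 560 would not.

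**The case against.** The strongest reply is that nothing in the design depends on 5000. Enrolment rests on capacity, 581 is computed without the benchmark, and no test or analysis uses it. That is correct. A reader might infer that 5000 justifies the sample size, but the text does not use it so. What remains is narrower: it is the comparator in the only adequacy statement for the primary endpoint.

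Second, 6207 is worded as a mean increase with a p-value against control, not as a between-arm effect, and that trial's SD and arm sizes are not given. This is fair, and it is why both readings are worked above. The planning SD also comes from Latino and African American participants together, while the earlier trial was in Latinos only. Even so, the mismatch is too large for a moderately different SD to remove.

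Third, a reader might infer that a unit or transcription error has been found. It has not. The sources for both figures are not at hand, and the article never expresses steps as a weekly total. The weekly reading would bring both figures into scale, which makes it worth checking and no more.

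Fourth, a reader might set the Discussion's remark that "even a modest stroke risk factor reduction in physical activity or blood pressure could have a tremendous population impact" against a 5000 threshold. There is no real conflict: that is a statement about a whole population, and it is compatible with a larger threshold for an individual.

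Finally, it is tempting to say that adequacy reverses. On the weekly assumption alone it does not, because 581 is still below 714. Reversal also needs the change-score figure at a low or moderate correlation.

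**Conclusion.** The point holds in this limited form. The adequacy statement for steps/day is not supported by the plan's own numbers. The benchmark is 184% of the stated mean and 2.28 of the stated SD, and the earlier trial's 6207 has the same problem of scale, so it cannot vouch for 5000.

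The 581 matches the mean of three measurements. For the change-score comparison named as primary, the detectable difference at 96 per arm is about 1,120 steps/day at the plan's correlation of 0.2, which is 1,120 / 581 = 1.9 times the stated figure. It equals or beats 581 only at a high correlation (560 at 0.8).

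These figures assume that SD 2190 applies at each visit and that the effective 96 per arm carries over unchanged to change scores. The finding about 6207 assumes an equal split and a similar SD in the earlier trial. If 5000 per day is confirmed at source, even 1,120 is well below it, but the article would still owe an explanation of how that threshold relates to a population averaging 2713. Enrolment and the planned tests are unaffected; what changes is what the trial can say about its sensitivity.

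**What to change.** 1. Check 5000 (reference 49) and 6207 (the earlier trial's report) against their sources, including the unit and, for 6207, whether it is a within-arm change or a difference between arms.
2. Restate the meaningful difference in steps/day on the scale of 2713 (SD 2190), with its rationale.
3. Replace the clause comparing 581 with 5000 by the detectable difference for the primary change-score comparison at 96 per arm, over a stated range of correlations (about 1,120 at 0.2, 886 at 0.5, 560 at 0.8), beside the checked benchmark. If 581 is kept, label it as the figure for the mean of three measurements.

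The cost is a source check and a few sentences, with no change to enrolment or analysis. The downside is that the statement of adequacy may become less favourable.
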